### Statistical analyses

#### Clinical effectiveness analyses

Non-inferiority of MPVC compared to CAU, concerning both mental and physical scores of the MSQOL-54 at 2 years follow-up, will be analyzed using confidence intervals (1-tailed 98.75% or equivalently 2-tailed 97.5%).

When a confidence interval excludes the pre-defined non-inferiority margin of 8 points, non-inferiority will be concluded. In the case of substantial potential confounding (unbalanced baseline variables) however, analysis will be based on testing for non-inferiority to enable adjustment. If non-inferiority is demonstrated, superiority will be studied subsequently.

Courses of Proms between the two study arms will be compared using analyses for longitudinal data.

Analysis of primary outcomes will be performed in the per-protocol analysis set. Additional analyses will be performed in the (modified) intention-to-treat analysis set.

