### Sample size, concerning the effectiveness analysis

The sample size was based on detecting non-inferiority concerning the two subscales of the MSQol-54, i.e. the mental score and the physical score, at 2 years of follow-up.

We adopted the standard deviation (SD) of the baseline data of the Dutch MS Study [47] (largest SD, concerning preliminary data). The minimal clinically (non)important change (MIC) was estimate in accordance with a distribution-based approach.

Sample size calculation was performed using IBM SPSS SamplePower 3.0. Calculation with delta 8 points, SD 17.5, alpha 0.0125 (1-sided), and power 80% resulted in *n* = 93 required participants per arm. To compensate for 10% dropout, *n* = 104 participants per arm will be included in this study.

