### Randomization

Stratified block randomization will be performed using the randomization module of our eCRF, ResearchManager (ResearchManager, Deventer, The Netherlands). ResearchManager is certified with ISO 27001 and NEN7510 and is affiliated with the 21 CFR part 11 FDA, which describes the administration of electronic records in a quality medical system of a medical device company.

Two strata will be used, i.e. sex and type of MS (RRMS, SPMS and PPMS). Distributions will be based on the known distributions in the Netherlands.

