### Missing data

Missing data will be managed by using modern techniques for the analyses of longitudinal data (Mixed Model analyses or Generalized Estimating Equations analyses).

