### Cost effectiveness analyses

Economic evaluations compare additional costs and additional outcomes of CAU to MPVC. This economic evaluation will involve a combination of a cost-effectiveness analysis (CEA) and a cost-utility analysis (CUA). In a CEA effects are presented in clinical outcomes. The primary outcome measure for the cost-utility analysis will be QALYs, based on the Euroqol utility scores [55]. In the CUA, the Incremental cost-effectiveness ratio (ICER) will be expressed as the incremental costs per QALY. This economic evaluation will be performed from a societal perspective, which implies that all relevant costs and outcomes will be taken into account. The economic evaluation study will be performed in accordance with the Dutch Guidelines of the National Health Care Institute [56].

Following the Dutch guidelines, an annual discount rate of 1.5% will be applied to the effects, and future costs will be discounted to their present value by a rate of 4% [56]. Our primary (base-case analyses) will be performed in accordance with the intention-to-treat principle, including data from all participants regardless of whether they received the intervention or not.

A baseline analysis will be performed to examine the comparability of groups at baseline for both costs and outcomes. If necessary, methods will be applied to check for differences at baseline [57]. To investigate whether data are normally distributed, a Kolmogorov-Smirnov test will be performed. Despite the usual skewness in the distribution of costs, the arithmetic means will be generally considered the most appropriate measures to describe cost data [58, 59]. Therefore arithmetic means (and standard deviations) will be presented. In case of skewness of the cost data, non-parametric bootstrapping will be used to test for statistical differences in costs between the intervention and control group. Non-parametric bootstrapping is a method based on random sampling with replacement based on individual data of the participants. The bootstrap replications will be used to calculate 95% confidence intervals around the costs (95% CI), based on the 2.5th and 97.5th percentiles.

The incremental cost-effectiveness ratio (ICER) will be determined based on the incremental costs and effects of intervention and control groups. The cost-effectiveness ratio will be expressed in terms of cost per outcome gained, the cost-effectiveness ratio will focus on the net cost per QALY gained.

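### Covariate adjustment of the primary non-inferiority comparison depends on undefined baseline imbalance, which leaves the primary model open and gives up precision

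*Protocol article*

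**What the plan says.** All references are to the protocol article.

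- **Clinical effectiveness analyses, default.** The mental and physical MSQOL-54 scores at 2 years are compared by confidence intervals, one-sided 98.75% or equivalently two-sided 97.5%. The decision rule is "When a confidence interval excludes the pre-defined non-inferiority margin of 8 points, non-inferiority will be concluded". No covariate is named.
- **Clinical effectiveness analyses, exception.** "In the case of substantial potential confounding (unbalanced baseline variables) however, analysis will be based on testing for non-inferiority to enable adjustment". The text does not say what counts as substantial, which variables are examined, or which model follows.
- **Sample size.** "Calculation with delta 8 points, SD 17.5, alpha 0.0125 (1-sided), and power 80% resulted in" 93 per arm, or 104 after allowing for 10% dropout. On the SD: "We adopted the standard deviation (SD) of the baseline data of the Dutch MS Study". No correlation between baseline and follow-up enters the calculation.
- **Randomization.** Allocation is stratified by sex and by MS type (RRMS, SPMS, PPMS). The strata return only under Subgroup analyses, as stratified analyses.
- **Tables 2 and 3.** MSQOL-54 is scheduled at baseline and at 6, 12, 18 and 24 months in both arms.
- **Missing data.** The methods named are "Mixed Model analyses or Generalized Estimating Equations analyses". The text does not say that either one supplies the 24-month contrast, or that the baseline score is a covariate.

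**The concern.** The rule lets the observed baseline data decide which model gives the primary answer. Because the trigger is undefined, two analysts following the text could report different primary results for the same scale. The trial is open label and its primary outcome is patient-reported, so that choice should not remain open once data are in hand.

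The stated reason for the switch does not hold either. Adjustment does not require giving up the interval: a model with covariates gives an adjusted difference and a confidence interval, which can be set against 8 points in the same way.

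Waiting for visible imbalance also misses the main benefit of adjustment. A baseline score that predicts the 24-month score reduces residual variance whether or not the arms happen to differ at baseline. Most trials following this rule would show no notable imbalance and would lose that benefit.

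**Working it through.** **1. Reproduce the plan's figure.** Inputs from the Sample size section: margin 8, SD 17.5, one-sided alpha 0.0125, power 80%, true difference 0.

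- Normal approximation: n = 2 × 17.5² × (2.2414 + 0.8416)² / 8² = 612.5 × 9.505 / 64 = 90.96, so 91 per arm.
- Two-sample noncentral t: power is 0.799 at 92 per arm and 0.804 at 93, so 93 per arm, as stated.
- Dropout: 93 / 0.90 = 103.3, so 104, as stated.

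The stated number is therefore that of an unadjusted two-sample comparison.

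**2. Unadjusted interval.** SE = 17.5 × √(2/93) = 2.566. With t(0.9875; 184 df) = 2.260, the half-width is 2.260 × 2.566 = 5.80 points.

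**3. Interval always adjusted for baseline.** Let r be the correlation of baseline with 24-month MSQOL-54. The documents do not give it, so a range is assumed. Residual SD = 17.5 × √(1 − r²). Half-width = 2.260 × residual SD × √(2/93). Power is by noncentral t with noncentrality 8 / SE.

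| r | Residual SD | Half-width | Power per scale | n per arm for 80% (normal approx.) |
|---|---|---|---|---|
| unadjusted | 17.5 | 5.80 | 80% | 91 |
| 0.3 | 16.7 | 5.53 | 84% | 83 |
| 0.5 | 15.2 | 5.02 | 91% | 69 |
| 0.7 | 12.5 | 4.14 | 98% | 47 |

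A small allowance for chance imbalance and the lost degree of freedom gives 5.55, 5.04 and 4.15, with the same rounded power. Since 1/√(1 − r²) is 1.05, 1.15 and 1.40, the unadjusted interval is about 5%, 15% or 40% wider than the adjusted one. The gain vanishes only for r of about 0.1 or less.

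**4. The switch itself.** The protocol gives no trigger, so two were assumed: adjust only if the baseline score differs between arms at p < 0.05, or at p < 0.20. Simulation used 93 per arm, with 100,000 runs for size (true difference −8) and 40,000 for power (true difference 0). Nominal size is 0.0125.

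| r | Trigger | Size of switch | Power of switch | Power, always adjusted |
|---|---|---|---|---|
| 0.3 | p < 0.05 | 0.0114 | 0.80 | 0.84 |
| 0.3 | p < 0.20 | 0.0110 | 0.81 | 0.84 |
| 0.5 | p < 0.05 | 0.0103 | 0.81 | 0.91 |
| 0.5 | p < 0.20 | 0.0080 | 0.84 | 0.91 |
| 0.7 | p < 0.05 | 0.0075 | 0.82 | 0.98 |
| 0.7 | p < 0.20 | 0.0050 | 0.87 | 0.98 |

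A mechanical trigger makes the test conservative and loses most of the available power. The simulation treats imbalance as chance. It covers neither a discretionary choice between the two analyses nor imbalance created by exclusions from the per-protocol set, which is the primary analysis set.

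**The case against.** The strongest reply is that the design is coherent on its own inputs. The number of patients was planned for an unadjusted comparison and reproduces at 80% power, so the lost precision is a forgone gain and not an error. That stands. It is also true that the article never calls the default interval unadjusted; this is inferred from the contrast drawn in the exception and from the raw SD. The mixed model named under Missing data could include the baseline score, so it would be too strong to say that the plan discards it. What can be said is that its use in the primary comparison is not stated.

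A second reply is that covariate lists and model terms belong in the SAP. That is right for the detail. But the article does more than leave the model open: it states a rule that makes adjustment depend on observed imbalance. An SAP that defined the threshold would still leave the primary analysis dependent on the data.

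Several stronger readings are tempting, and the documents do not support them:

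- **Inflated risk of a false non-inferiority claim.** The simulated switch had size below nominal. Discretionary choice between analyses remains a reasonable worry, but it has not been quantified.
- **A standard error made materially too large by omitting the strata.** The documents do not show how strongly sex and MS type predict MSQOL-54, so no size can be given.
- **A fault in allowing GEE.** Choosing between GEE and a mixed model is ordinary SAP detail, and the text does not tie either to the primary contrast.
- **The same defect in the economic evaluation.** The statement "If necessary, methods will be applied to check for differences at baseline" rests on a cited source that is not at hand, and it does not show how QALYs will be adjusted.

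**Conclusion.** The point holds as one of pre-specification and efficiency. The article makes adjustment of the primary comparison conditional on an undefined imbalance and attaches an unnecessary change from interval to test. The undefined rule is plain from the text and needs no assumption.

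The size of the precision loss rests on an assumed r, on an SD of 17.5 at 24 months, and on 93 evaluable patients per arm. Over r = 0.3 to 0.7 the avoidable extra half-width runs from about 0.3 to 1.7 points (5.80 − 5.53 to 5.80 − 4.14), and the forgone power per scale from about 4 to 18 percentage points. At the low end the gain is modest. Only its direction is firm, for r above about 0.1. The change should be made, but the trial is not invalid without it.

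**What to change.** In Clinical effectiveness analyses, delete the imbalance trigger and the switch to a test. For each MSQOL-54 summary score, pre-specify one model that is always adjusted for the baseline score, sex and MS type. The mixed model already named under Missing data would serve, fitted to the 6-, 12-, 18- and 24-month scores. Read non-inferiority from the adjusted 24-month difference and its two-sided 97.5% confidence interval against the 8-point margin. An unadjusted interval may be kept as a labelled sensitivity analysis. Remaining model detail can go in the SAP.

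The cost is wording only: the baseline score is scheduled in both arms, the strata are known from randomization, and the sample size need not change. The change should be dated before outcomes are compared by arm.

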### Subgroup analyses

The effect of strata will be studied by stratified analyses.

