**Methods:**

A randomized, parallel-group, open label, non-inferiority trial will be conducted to compare MPVC with CAU in MS patients and their partners/informal caregivers. A total of 208 patients will be included with follow-up measurements for 2 years (at baseline and every 3 months). One hundred four patients will be randomized to MPVC and 104 patients to CAU. Partners/informal caregivers of both groups will be asked to participate.

The study will consist of three parts: 1) a clinical effectiveness study, 2) an economic evaluation, and 3) a process evaluation. The primary outcome relates to equal or improved disease-specific physical and mental quality of life of the MS patients. Secondary outcomes relate to self-efficacy, efficiency, cost-effectiveness, autonomy, satisfaction with the care provided, and quality of life of partners/informal caregivers.

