### Study population(s)

A total of 208 patients of all three types of MS, with or without their partner or informal caregiver will be included in the study (Tables 2 and 3). Most of the patients in the study have RRMS (relapses remitting, 80%), the least have PPMS (primary progressive, 8%) and the rest 10% SPMS (secondary progressive). This proportion corresponds to the prevalence of MS in the population of the Netherlands.

Inclusion criteria are 18 years of age or older, ability to understand Dutch and willingness and able to use MPVC.

Patients whose diagnosis of MS has not yet been clearly established or patients who have underlying diseases similar to MS in terms of symptoms (such as polyneuropathy, cerebral infarction, semi-lateral paralysis or other neurological diseases) will be excluded from participation.

The study team consists of the investigator, research nurse, the MS neurologist, and the MS nurse specialist.

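### Stratified analyses by sex and MS type do not estimate whether the MPVC effect differs between strata, and the SPMS and PPMS strata are too small to read on their own

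*Protocol article*

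**What the plan says.** Under Subgroup analyses, the protocol article has a single sentence: "The effect of strata will be studied by stratified analyses". The strata are defined under Randomization: "Two strata will be used, i.e. sex and type of MS (RRMS, SPMS and PPMS". Under Study population(s) the expected mix is given: "Most of the patients in the study have RRMS (relapses remitting, 80%), the least have PPMS (primary progressive, 8%) and the rest 10% SPMS". These shares add to 98%, so SPMS could be read as 10% or as the remaining 12%.

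The abstract gives the arm sizes: "One hundred four patients will be randomized to MPVC and 104 patients to CAU". The sample size section gives the planning values: "Calculation with delta 8 points, SD 17.5, alpha 0.0125 (1-sided), and power 80"%. It then allows for 10% dropout.

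Under Clinical effectiveness analyses, non-inferiority is concluded when the confidence interval (two-sided 97.5%) excludes a margin of 8 points on the MSQOL-54 summary scores at 2 years. That rule is written for the overall comparison of MPVC with CAU. The subgroup sentence sets no margin, test or verdict for individual strata.

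**The concern.** Whether the effect of MPVC depends on MS type or sex is a question about a difference between strata. An analysis repeated inside each stratum returns one estimate and one interval per stratum. It gives no estimate, interval or test of the difference between them. Comparing which intervals clear a threshold is no substitute, because interval width depends on stratum size.

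Here the MS-type strata differ in size by a factor of eight to ten. RRMS would have a usable interval, and the two progressive types would have intervals far wider than the margin. The risk is that a result shown in RRMS and not shown in SPMS or PPMS is taken to mean that MPVC does not suit progressive MS, when the pattern says little beyond the number of patients.

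**Working it through.** **Inputs.** From the protocol article: 104 per arm, SD 17.5, margin 8, one-sided alpha 0.0125, dropout 10%, and shares of 80% RRMS, 10% SPMS and 8% PPMS. Assumptions added here: the same SD in every type, equal allocation within type, the planned mix realised, a true difference of 0, and one summary score.

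**The plan's own figure.** With SE = SD × √(2/n) and a noncentral-t power calculation, power is 79.9% at n = 92 and 80.4% at n = 93 per arm. This reproduces 93. Then 93 / 0.9 = 103.3, rounded up to 104. The sample size is correct for the overall comparison.

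**Patients per arm by type.** n = 104 × share before dropout; multiply by 0.9 after dropout.

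| Type | Before dropout | After dropout |
|---|---|---|
| RRMS (80%) | 83.2 | 74.9 |
| SPMS (10%) | 10.4 | 9.4 |
| SPMS if 12% | 12.5 | 11.2 |
| PPMS (8%) | 8.3 | 7.5 |

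**Interval width and chance of clearing the margin, after dropout.** SE = 17.5 × √(2/n). Half-width = t(0.9875; 2n − 2) × SE. The chance of clearing the margin is noncentral-t power with noncentrality 8/SE.

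| Type | SE | t | Half-width | Chance |
|---|---|---|---|---|
| RRMS | 2.86 | 2.264 | 6.5 | 70.3% |
| SPMS (10%) | 8.09 | 2.462 | 19.9 | 9.3% |
| SPMS if 12% | 7.39 | 2.419 | 17.9 | 11.1% |
| PPMS | 9.04 | 2.533 | 22.9 | 7.5% |

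Without dropout the half-widths are 6.1, 18.7 (16.8 if SPMS is 12%) and 21.4 points, and the chances are 75%, 10% (12%) and 8%.

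**Pattern across types if the margin were applied in each.** The strata are independent and the effect is identical in all three.

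- RRMS passes and at least one progressive type fails: 0.703 × (1 − 0.093 × 0.075) = 0.698, about 70% (about 75% without dropout).
- RRMS passes and both fail: 0.703 × (1 − 0.093) × (1 − 0.075) = 0.590, about 59% (about 62% without dropout).
- All three pass: 0.703 × 0.093 × 0.075 = 0.005, about 0.5%.

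Reading SPMS as 12% leaves the first figure at about 70%.

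**What an interaction estimate can deliver.** SE of the difference in effect = 17.5 × √(2/n_RRMS + 2/n_other). The difference detectable with 80% power at two-sided 5% is (1.96 + 0.84) × SE.

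| Contrast | SE, full enrolment | Detectable | Detectable after dropout |
|---|---|---|---|
| RRMS vs SPMS | 8.1 | 22.8 | 24.0 |
| RRMS vs PPMS | 9.0 | 25.2 | 26.6 |
| RRMS vs SPMS and PPMS pooled | 6.3 | 17.7 | 18.7 |

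At full enrolment, power for a true 8-point interaction is between 14% (RRMS vs PPMS) and 24% (pooled). With identical effects, a 5% interaction test signals a difference in 5% of trials.

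**The case against.** The strongest objection is that the harm needs a step the article does not take. A reader might infer that non-inferiority will be declared or denied for each MS type against the 8-point margin. The documents do not support this: the decision rule is stated for the overall comparison, and the subgroup sentence fits stratum estimates with intervals just as well. This stands, so the 70% figure is conditional. It is also close to the RRMS pass rate alone, because failure of at least one progressive type is almost certain.

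A reader might also infer that small strata will show a different effect because they are small. They will not. The stratum estimates are unbiased; what changes with size is interval width, chance scatter and any pass or fail label. An interval of ±20 points shows its imprecision openly.

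Third, a stratified analysis can include a comparison across strata, and an article may leave the model form to the full protocol or SAP. This stands in part. The absence of an interaction term or of an exploratory label is not itself the point. The article does name a method, however, and under a heading on subgroups that method most naturally means one analysis per stratum. A pooled, stratum-adjusted estimate would not show an effect of strata either.

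Finally, no sex split is given, so nothing is shown about the size of the problem for sex, and the interaction estimate will itself be imprecise. Both are accepted.

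**Conclusion.** The point holds as a minor one. On its natural reading, the stated method does not address whether the MPVC effect differs by sex or MS type. For MS type the consequence can be sized: half-widths of about 6.5, 20 and 23 points in RRMS, SPMS and PPMS after dropout (about 18 for SPMS if it is 12%), against a margin of 8. Separate results in the progressive types could therefore say almost nothing about non-inferiority there, and a contrast with RRMS would mainly reflect precision.

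These figures rest on SD 17.5 in every type, equal allocation within type, the planned mix and 10% dropout. The primary set is per-protocol, so the numbers analysed may be smaller. The sample size and the primary conclusion are unaffected.

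**What to change.** Replace the sentence under Subgroup analyses with:

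> Effect modification by MS type and by sex is assessed in one model on all patients, with baseline score, the stratification factors and treatment-by-stratum interaction terms; interaction estimates are reported with CIs. Stratum-specific estimates are exploratory and descriptive, and no non-inferiority verdict is given per stratum.

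The cost is one extra model on data already being collected. No non-inferiority claim per MS type can then be made, but 7 to 11 analysed patients per arm in a progressive type could not support one. Power for the interaction is low, with detectable differences of about 18 to 27 points, so the report should say that a non-significant interaction is not evidence of equal effects.

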### Missing data

Missing data will be managed by using modern techniques for the analyses of longitudinal data (Mixed Model analyses or Generalized Estimating Equations analyses).

### Cost effectiveness analyses

Economic evaluations compare additional costs and additional outcomes of CAU to MPVC. This economic evaluation will involve a combination of a cost-effectiveness analysis (CEA) and a cost-utility analysis (CUA). In a CEA effects are presented in clinical outcomes. The primary outcome measure for the cost-utility analysis will be QALYs, based on the Euroqol utility scores [55]. In the CUA, the Incremental cost-effectiveness ratio (ICER) will be expressed as the incremental costs per QALY. This economic evaluation will be performed from a societal perspective, which implies that all relevant costs and outcomes will be taken into account. The economic evaluation study will be performed in accordance with the Dutch Guidelines of the National Health Care Institute [56].

Following the Dutch guidelines, an annual discount rate of 1.5% will be applied to the effects, and future costs will be discounted to their present value by a rate of 4% [56]. Our primary (base-case analyses) will be performed in accordance with the intention-to-treat principle, including data from all participants regardless of whether they received the intervention or not.

A baseline analysis will be performed to examine the comparability of groups at baseline for both costs and outcomes. If necessary, methods will be applied to check for differences at baseline [57]. To investigate whether data are normally distributed, a Kolmogorov-Smirnov test will be performed. Despite the usual skewness in the distribution of costs, the arithmetic means will be generally considered the most appropriate measures to describe cost data [58, 59]. Therefore arithmetic means (and standard deviations) will be presented. In case of skewness of the cost data, non-parametric bootstrapping will be used to test for statistical differences in costs between the intervention and control group. Non-parametric bootstrapping is a method based on random sampling with replacement based on individual data of the participants. The bootstrap replications will be used to calculate 95% confidence intervals around the costs (95% CI), based on the 2.5th and 97.5th percentiles.

The incremental cost-effectiveness ratio (ICER) will be determined based on the incremental costs and effects of intervention and control groups. The cost-effectiveness ratio will be expressed in terms of cost per outcome gained, the cost-effectiveness ratio will focus on the net cost per QALY gained.

The ICER is calculated as follows. ICER = (Ci - Cc) / (Ei - Ec), where Ci is the annual total cost of both study groups, Cc is the annual total cost of the control group (treatment by usual means), Ei is the effect at three-year follow-up for the intervention and control group, and Ec is the effect at the last follow-up for the control group (treatment by usual means).

The robustness of the ICER will be checked by non-parametric bootstrapping. Bootstrap simulations will also be conducted in order to quantify the uncertainty around the ICER, yielding information about the joint distribution of cost and effect differences. The bootstrapped cost-effectiveness ratios will be subsequently plotted in a cost-effectiveness plane, in which the vertical line reflects the difference in costs and the horizontal line reflects the difference in effectiveness. The choice of treatment depends on the maximum amount of money that society is prepared to pay for a gain in effectiveness, which is called the ceiling ratio. Therefore, the bootstrapped ICERs will also be depicted in a cost-effectiveness acceptability curve showing the probability that intervention and control groups are cost-effective using a range of ceiling ratios. In The Netherlands, a ceiling ratio between at € 20,000, € 50,000 and € 80,000 per QALY exists, depending on the burden of disease [60].

Additionally, to demonstrate the robustness of our base-case findings, a multi-way sensitivity analysis will be performed. In the sensitivity analysis uncertain factors of assumptions in the base case analysis will recalculated in order to assess whether the assumptions have influenced the incremental cost-effectiveness ratio (ICER), for example by varying cost-prices and volumes between minimum and maximum [61].

